# MR-guided adaptive versus ITV-based stereotactic body radiotherapy for hepatic metastases (MAESTRO): a randomized controlled phase II trial

**DOI:** 10.1186/s13014-022-02033-2

**Published:** 2022-03-27

**Keywords:** Liver metastases, Stereotactic body radiotherapy (SBRT), MR-guided radiotherapy, MR-Linac, MRI, ITV, Adaptive radiotherapy (ART), Radiation-induced liver disease (RILD), Stereotactic ablative radiotherapy (SABR), Stereotactic Magnetic Resonance Guided Radiation Therapy (SMART)

## Abstract

**Background:**

Stereotactic body radiotherapy (SBRT) is an established local treatment method for patients with hepatic oligometastasis or oligoprogression. Liver metastases often occur in close proximity to radiosensitive organs at risk (OARs). This limits the possibility to apply sufficiently high doses needed for optimal local control. Online MR-guided radiotherapy (oMRgRT) is expected to hold potential to improve hepatic SBRT by offering superior soft-tissue contrast for enhanced target identification as well as the benefit of gating and daily real-time adaptive treatment. The MAESTRO trial therefore aims to assess the potential advantages of adaptive, gated MR-guided SBRT compared to conventional SBRT at a standard linac using an ITV (internal target volume) approach.

**Methods:**

This trial is conducted as a prospective, randomized, three-armed phase II study in 82 patients with hepatic metastases (solid malignant tumor, 1–3 hepatic metastases confirmed by magnetic resonance imaging (MRI), maximum diameter of each metastasis ≤ 5 cm (in case of 3 metastases: sum of diameters ≤ 12 cm), age ≥ 18 years, Karnofsky Performance Score ≥ 60%). If a biologically effective dose (BED) ≥ 100 Gy (α/β = 10 Gy) is feasible based on ITV-based planning, patients will be randomized to either MRgRT or ITV-based SBRT. If a lesion cannot be treated with a BED ≥ 100 Gy, the patient will be treated with MRgRT at the highest possible dose. Primary endpoint is the non-inferiority of MRgRT at the MRIdian Linac® system compared to ITV-based SBRT regarding hepatobiliary and gastrointestinal toxicity CTCAE III or higher. Secondary outcomes investigated are local, locoregional (intrahepatic) and distant tumor control, progression-free survival, overall survival, possible increase of BED using MRgRT if the BED is limited with ITV-based SBRT, treatment-related toxicity, quality of life, dosimetric parameters of radiotherapy plans as well as morphological and functional changes in MRI. Potential prognostic biomarkers will also be evaluated.

**Discussion:**

MRgRT is known to be both highly cost- and labor-intensive. The MAESTRO trial aims to provide randomized, higher-level evidence for the dosimetric and possible consecutive clinical benefit of MR-guided, on-table adaptive and gated SBRT for dose escalation in critically located hepatic metastases adjacent to radiosensitive OARs.

***Trial registration*:**

The study has been prospectively registered on August 30th, 2021: Clinicaltrials.gov, “Magnetic Resonance-guided Adaptive Stereotactic Body Radiotherapy for Hepatic Metastases (MAESTRO)”, NCT05027711.

**Supplementary Information:**

The online version contains supplementary material available at 10.1186/s13014-022-02033-2.

## Background

Standard therapy for patients with hepatic oligometastases is surgical resection. Hepatic metastasectomy has been performed for more than 3 decades with 5-year survival rates of 50–60% and up to 20% long-term survivors [1–4]. However, only 15–20% of patients with hepatic oligometastases are initially eligible for such a radical surgical approach due to an unresectable tumor location, inadequate hepatic reserve or other comorbidities [5, 6]. For the majority of patients who are not amenable for surgery, alternative liver-directed therapies are offered for providing local control and potentially superior overall survival, e.g. radiofrequency ablation, microwave ablation, transarterial chemoembolization, cryoablation, high-dose-rate brachytherapy or stereotactic body radiotherapy (SBRT) [7, 8].

Following hepatic irradiation, radiation-induced liver disease (RILD) is a potential complication [9, 10]. Nevertheless, due to its parallel architecture model of radiobiology, the liver can tolerate high doses to small volumes as long as the mean dose to the uninvolved hepatic tissue is kept below the threshold for severe RILD. For single doses of 1.5 Gy bidaily and α/β = 2 Gy, threshold mean liver doses of 30–32 Gy correspond to respective biologically effective doses (BEDs) of 52.5–55.1 Gy [11]. Further potential severe side-effects include gastric and bowel ulcers or perforations and chest wall fibrosis and necrosis. Overall, severe toxicities ≥ grade III can occur in up to 12 to 35% of patients undergoing liver SBRT [12, 13].

More recently, technological advances in target definition, treatment planning and methods of image guidance have enabled precise local ablative treatments of small hepatic lesions by applying SBRT. SBRT allows for safe delivery of large single doses of highly conformal radiation with steep dose gradients to the surrounding healthy tissue over a limited number of fractions. Due to its spatial precision, SBRT permits the administration of tumoricidal radiation doses to hepatic metastases, while sparing organs at risk (OARs) including the surrounding healthy hepatic tissue and hence lowering toxicity. Several retrospective and prospective series reported 1- and 3-year local control (LC) rates of 56–100% and 45–100% following SBRT for liver metastases, respectively [12, 14–18]. Similar to pulmonary SBRT, a dose–response relationship is assumed for hepatic SBRT [14, 18]. A recent meta-analysis by Ohri et al. reported significantly superior 3-year LC of 93% for hepatic metastases treated with biologically effective doses (BEDs) exceeding 100 Gy than for those irradiated with BEDs < 100 Gy with 3-year LC of only 65% [18]. However, metastases in close proximity to organs at risk (OARs) (stomach, duodenum, bowel) as well as large central metastases often cannot be treated with sufficiently high doses due to the increased risk of toxicity [19–21]. The applied maximum dose to the stomach and the bowel is known to significantly correlate with the risk of severe gastrointestinal toxicity [22]. Hence, currently only lower total doses have been applied for such lesions reducing the possibility of long-term local control.

Abdominal organs such as the liver and respective tumors are subject to movement caused by breathing and positional drifts in the body of several centimeters during treatment [23–26]. Motion management strategies are therefore crucial for a precise and safe application of high-dose liver SBRT. Clinically established strategies for motion compensation include breath hold techniques or continuous irradiation in free breathing with an internal target volume (ITV) [12, 27, 28]. The ITV concept, which is most widely used, accounts for tumor movement by incorporating tumor motion on several breathing phases assessed by a 4-dimensional (4D) CT [29]. As long as fraction times do not exceed a certain time and sufficient margins are provided, the ITV can be regarded as a robust concept for the consideration of tumor motion [30].

In routine clinical practice, low dose computed tomography scans (“cone-beam CT” (CBCT)) are generally used for daily image guidance of patient positioning, tumor location and alterations in patient anatomy (image-guided radiotherapy, IGRT). However, image-guidance for hepatic SBRT is challenged due to low tumor visibility in CBCT images and related soft tissue contrast. Consequently, for precisely targeting hepatic metastases, some centers invasively implant fiducial markers in the liver near the tumor for topographic orientation [31]. Furthermore, daily application of CBCTs is accompanied by the exposure of an additional amount of radiation dose, which in turn might theoretically even lead to an increased risk of secondary malignancies [32]. For treatment planning, magnetic resonance imaging (MRI) has gained a fundamental role in daily clinical practice, especially with regard to detecting and characterizing abdominal malignancies, such as hepatobiliary cancer and liver metastasis [33]. MRI with its superior soft tissue contrast enhances tumor delineation by enabling superior distinction between cancerous and normal tissues [34]. Additionally, functional MRI with modern, optimized sequences allows for non-invasive assessment of tissue perfusion, diffusion or cellular density, exceeding the morphological characterization of conventional MRI [35, 36].

MR-guided radiotherapy (MRgRT) has recently become clinically available, providing an excellent soft tissue contrast for precise detection of the tumor position and potential daily changes in patient anatomy without additional radiation dose [37, 38]. MR-guidance further offers the possibility to visualize tumor volume and nearby OARs during the whole treatment session (cine MRI). Safety margins and hence the irradiated volume can be decreased for hepatic MR-guided SBRT, thereby reducing the risk of potential toxicity [39, 40]. Hepatic SBRT of smaller target volumes might offer the possibility of dose escalation for increasing local control.

MRgRT further allows for online plan adaptation in response to specific changes in tumor and OAR anatomy that may occur during the course of treatment. In conventional radiotherapy, one treatment plan is generated based on the patient anatomy during simulation CT imaging. However, significant organ motion is known to occur between different treatment fractions, e.g. due to varying filling of hollow organs or tumor shrinkage in response to therapy (interfractional organ motion) [41, 42]. MRgRT enables daily imaging of sufficient quality to permit immediate plan adjustments in response to the anatomy of the day, while the patient keeps lying on the treatment couch [37, 43–45]. Online plan adaptation allows for superior sparing of OARs and offers the possibility for dose escalation hereby potentially improving local control rates [40, 44]. Particularly for hepatic metastases located near the liver margin, superior visualization before and during irradiation allows a safe treatment with high doses near organs such as bowel or stomach, where positional uncertainties could result in a dose that exceeds OAR tolerance [46]. With real-time imaging, treatment plans for hepatic metastases can be adapted as needed and RT doses may be better personalized.

Consequently, oncologic treatments with hybrid MRI-Linear accelerators might improve treatment outcome both with regard to tumor response and treatment related side effects, as for the possibility of monitoring treatment related changes by different morphologic and functional MRI sequences.

Up to now, studies for MRgRT of hepatic lesions are scarce with mainly retrospective analyses, observational studies and small case series, limited to a maximum of 21 patients with liver metastases per study [39, 40, 46–52]. However, MRgRT is very staff-intense and time-consuming compared to standard CT-guided hepatic SBRT [53, 54]. Hence, prospective studies are needed to assess which patients profit most from this new technique. The aim of the present study is therefore to evaluate potential benefits of MRgRT compared to ITV-based SBRT as one of the current, and probably the most widely-used, state-of-the-art standard techniques. Non-inferiority of MRgRT compared to standard ITV-based SBRT for hepatic metastases will be evaluated in respect to gastrointestinal and hepatobiliary toxicity ≥ grade III. Special attention will be paid to whether MRgRT offers a potential for dose escalation in case of critical proximity of hepatic metastases to gastrointestinal OARs, currently limiting application of a sufficient BED of ≥ 100 Gy in certain cases.

## Methods/design

### Trial aim

The MAESTRO trial compares online adaptive MR-guided SBRT with state-of-the-art ITV-based SBRT of hepatic metastases to strive for prospective, randomized evidence regarding toxicity as well as potential dosimetric and clinical advantages of oMRgRT for dose escalation in critically located hepatic metastases adjacent to radiosensitive OARs.

### Trial design

The MAESTRO trial is a multi-center, prospective three-armed phase II study. It has been designed by the study initiators at the Department of Radiation Oncology of the University of Heidelberg. The trial is performed at the University of Heidelberg, Department of Radiation Oncology and at University Hospital, LMU Munich, Department of Radiation Oncology. Further study sites might be included. A list of study sites can be obtained from the corresponding author on request. The University of Heidelberg is responsible for the coordination and trial management, as well as quality assurance including reporting, monitoring and database management. The current version of the study protocol is version 1.4 from November, 19th 2021 (Additional file 1). The study workflow and treatment arms are depicted in Fig. 1. At least 82 patients fulfilling the inclusion criteria will be enrolled.

**Fig. 1 Fig1:**
[figure not shown]
Trial flow-chart

### Inclusion criteria

Patients with hepatic metastases of a solid malignant non-hepatic primary tumor (no hepatocellular or cholangiocellular carcinoma, no germ cell tumor, leukemia or lymphoma) meeting all of the following criteria are considered for admission to the trial:1–3 Active hepatic metastases confirmed by pre-therapeutic MRIIndication for SBRT of 1–3 hepatic metastasesMaximum diameter of each hepatic metastasis ≤ 5 cm (in case of 3 metastases: sum of diameters ≤ 12 cm)Age ≥ 18 years of ageKarnofsky Performance Score ≥ 60% / ECOG grade 0–2Ability to lie still on the radiotherapy treatment couch for at least one hourAbility to hold one’s breath for more than 25 sFor women with childbearing potential, adequate contraceptionAbility of subject to understand character and individual consequences of the clinical trialWritten informed consent (must be available before enrolment in the trial).

### Exclusion criteria

Patients presenting with any of the following criteria will not be included in the trial:Patients after liver transplantationImpairment of liver function to an extent contraindicating radiotherapy (to the discretion of the treating radiation oncologist)Active acute hepatic/biliary infection (e.g. hepatitis, cholangitis, cholecystitis)Previous radiotherapy of the hepatobiliary system, if previous and current target volumes overlapPatients who have not yet recovered from acute toxicities of prior therapiesClaustrophobiaPregnant or lactating women

Contraindications against performing contrast-enhanced MRI scans (pacemakers or other implants making MRI impossible, allergy to gadolinium-based contrast agent)

Participation in another competing clinical study or observation period of competing trials

Concomitant systemic therapy or other anti-tumor medication are not part of the study treatment and are only allowed after consultation with the treating radiation oncologist.

All patients receive a pre-treatment hepatic MRI for diagnostic and treatment planning purposes.

### Randomization

Patients are randomized according to initial treatment planning. If a BED ≥ 100 Gy can be achieved with standard ITV-based planning, patients are randomized to MRgRT (arm A) or ITV-SBRT (arm B) in a 1:1 fashion. If a BED ≥ 100 Gy (α/β = 10 Gy) cannot be achieved with ITV-SBRT planning, the patient is treated with the highest possible dose using MRgRT (arm C). To achieve comparable intervention groups (arms A and B), patients are allocated in a concealed fashion in a 1:1 ratio by means of randomization using a centralized web-based tool (www.randomizer.at). Randomization is stratified with respect to the factor center. Block randomization with varying block lengths will be performed to achieve in total equal group sizes for randomization.

### Treatment planning and dose prescription

Patient eligibility for SBRT is tested before enrollment in the trial. Training aims to enhance the ability to follow respiratory instructions including free breathing and deep inspiration breath-hold.

In a first step, treatment planning is performed with contrast-enhanced and non-enhanced CT scans in free breathing in a supine position. Furthermore, patients undergo a 4D-CT with typically 8 phases to assess tumor motion in free-breathing. Patients are immobilized according to standard practice in the specific center. Based on pre-therapeutic MRI and planning CT, SBRT is planned using an internal target volume (ITV) concept. Target volume delineation for ITV-based SBRT is performed as follows:Gross tumor volume (GTV): macroscopic, contrast-enhanced tumor in the planning MRI and, if definable, in the planning CTInternal Target Volume (ITV): sum of all GTV contours derived from different breathing phases assessed via 4D-CTClinical Target Volume (CTV): ITV + 5 mmPlanning Target Volume (PTV): CTV + at least 5 mm, depending on the applied image-guidance (e.g. CBCT)

Dose is prescribed to the surrounding 65–95% isodose (preferably: 65–80% isodose) in up to 10 fractions. For hepatic metastases, α/β = 10 Gy is assumed. Dose constraints for OARs are summarized in Table 1. These dose constraints resemble UK Consensus on Normal Tissue Dose Constraints for Stereotactic Radiotherapy [55]. Further dose constraints of normal tissue are respected according to German and international guidelines [12, 55, 56]. If a BED of ≥ 100 Gy can be achieved with an ITV-concept, patients are randomized to arms A or B. If a BED of ≥ 100 Gy is not achievable using an ITV approach, patients are treated with MRgRT in arm C without randomization.

**Table 1 Tab1:** Dose constraints for organs at risk depending on fractionation

Organ at risk	Dose constraints (Gy)				
Number of fractions	3 Fractions	5 Fractions	6 Fractions	8 Fractions	10 Fractions
Uninvolved liver (= liver-CTV) ≥ 700 cm^3^	< 19.2	< 24	< 26	< 29	< 32
Stomach D_0.5cm3_	< 22.2	< 35	< 37	< 40	< 43.5
Duodenum D_0.5cm3_	< 22.2	< 35	< 37	< 40	< 43.5
Bowel D_0.5cm3_	< 25.2	< 35	< 37	< 40	< 43.5
Sigma/Rectum D_0.5cm3_	< 28.2	< 34	< 37	< 41	< 44.0
Esophagus D_0.5cm3_	< 25.2	< 34	< 36	< 40	< 43.5
Heart D_0.5cm3_	< 25.0	< 29.0	< 31.5	< 60.0	< 66.0
Kidneys Mean dose	< 8.5	< 10.0	< 10.8	< 11.5	< 12.0
Spinal cord D_0.1cm3_	< 21.6	< 27.0	< 29.0	< 32.0	< 35.0

CTV, clinical target volume; D_xcm3_, dose which is received by less than × cm^3^

In a second step, patients to be treated with MRgRT receive a simulation at the MR-Linac for MRgRT planning. If necessary, they also undergo a specific planning CT in deep-inspiration breath-hold (non-contrast-enhanced). In the MRgRT arms, patients are immobilized in supine position, and fitted with the MRI receiver coils.

For MRgRT (arms A and C), target volume delineation is performed as follows:Gross tumor volume (GTV): macroscopic, contrast-enhanced tumor in the planning MR and, if definable, in the planning CTClinical Target Volume (CTV): GTV + 5 mmPlanning Target Volume (PTV): CTV + 3 mm

Dose prescription and constraints for MRgRT are the same as for ITV-based SBRT as described above. In arm A, a BED of ≥ 100 Gy must be prescribed. In arm C, patients are treated via MRgRT with the highest achievable dose as deemed by the treating radiation oncologist.

For MRgRT (arms A and C), daily OAR contour adaption is performed within the region PTV_expand_ slightly adapted from the recommendations by Bohoudi et al. [44]. The PTV_expand_ is the PTV enlarged by 3 cm in medio-lateral and anterior–posterior direction as well as 1 cm in the cranio-caudal direction. The need to adapt the treatment plan is decided upon by the treating physician based on dose prediction. For MRgRT, real-time cine MR imaging is used for respiratory gating. Gating thresholds are defined by the treating physician.

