### Trial objectives

The primary endpoint is defined as the occurrence of treatment-related gastrointestinal or hepatobiliary toxicity of grade III or higher according to Common Terminology Criteria for Adverse Events (CTCAE) V5.0 assessed within the first year after SBRT. The primary aim of the study is the assessment of non-inferiority of MRgRT to ITV-SBRT regarding the primary endpoint, assuming a non-inferiority margin of $$\delta =10\%.$$ Toxicity of CTCAE III° or higher is generally low, between below 1% [57] and 7.7% [46] according to published literature. Therefore, a non-inferiority-margin of $$\updelta$$=10% is deemed adequate.

Secondary objectives include further toxicity according to CTCAE V5.0, quality of life according to EORTC QLQ C-30 and EORTC QLQ LMC-21, local control (treated lesions), locoregional control (whole liver), distant tumor control, progression-free survival (PFS) and overall survival (OS).

QoL will be measured with the help of the validated 30-item self-assessment questionnaire of the European Organization for Research and Treatment of Cancer (EORTC QLQ-C30, version 3.0). It is composed of five multi-item functional scales (physical, role, emotional, cognitive, and social function), three multi-item symptom scales (fatigue, pain, nausea/vomiting) combined with a global health and quality-of life scale. The other six single items assess further symptoms (dyspnea, insomnia, appetite loss, constipation and diarrhea) that are often reported by cancer patients as well as financial difficulties [58]. The QLQ-C30 questionnaire will be complemented with the colorectal liver cancer module of the EORTC (QLQ-LMC-21), initially designed for patients with colorectal liver metastases [59, 60]. QLQ-LMC-21 comprises another 21 items in five scales (nutritional, fatigue, pain, emotional) and six single items assessing further symptoms (weight, loss of taste, xerostomia, oral mucositis, paresthesia, jaundice).

For patients in the MRgRT arms, an in-house developed patient-reported questionnaire will be applied after the first fraction of radiotherapy and at the end of radiotherapy to assess acceptance of MR-guided radiotherapy [53]. The questionnaire consists of questions regarding potential MR-related experiences and complaints (e.g. noise, bore size, fixation with coils). Furthermore, the perception of their active role during gated dose delivery SBRT is assessed. Items are scored using a 5-point scale.

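### Table 1's heart dose limits are not coherent across fractionation schedules: the limit nearly doubles between 6 and 8 fractions, and the permitted dose per fraction rises where it falls in every other row

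*Protocol article*

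**What the plan says.** The section on treatment planning and dose prescription allows a range of schedules: "Dose is prescribed to the surrounding 65–95% isodose (preferably: 65–80% isodose) in up to 10 fractions". Table 1 gives organ-at-risk limits for five of them ("Number of fractions 3 Fractions 5 Fractions 6 Fractions 8 Fractions 10 Fractions"). The heart row reads "Heart D_0.5cm3_ < 25.0 < 29.0 < 31.5 < 60.0 < 66.0", in Gy, with the same dose-volume measure in every column.

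On the source, the section says: "These dose constraints resemble UK Consensus on Normal Tissue Dose Constraints for Stereotactic Radiotherapy". It adds that further constraints follow German and international guidelines. The note under the table only explains abbreviations: "CTV, clinical target volume; D_xcm3_, dose which is received by less than × cm^3". The limits bind in every arm: "Dose prescription and constraints for MRgRT are the same as for ITV-based SBRT as described above". For the full protocol, the trial design section states: "The current version of the study protocol is version 1.4 from November, 19th 2021 (Additional file 1").

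**The concern.** A limit for a longer schedule normally allows more total dose but less dose per fraction. Eight of the nine rows of Table 1 follow that pattern throughout. The heart row follows it from 3 to 6 fractions, breaks it between 6 and 8, and resumes it from 8 to 10. The two groups of heart entries therefore look like two different standards of protection.

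At stake is a stated safety limit used for planning in all arms. If the 8- and 10-fraction entries are too high, plans in those schedules for lesions near the heart could give the heart more dose than intended. If the 3- to 6-fraction entries are too strict, nobody receives excess dose, but plans are restricted without need.

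**Working it through.** **Inputs.** All limits and fraction numbers come from Table 1. The α/β of 10 Gy for metastases and the BED threshold of 100 Gy come from the same section. The article gives no α/β for the heart, so a range of 2 to 10 Gy is assumed in step 5 only. The limits are tabulated without a derivation, so there is no calculation of the plan's own to reproduce.

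**Step 1: dose per fraction = limit / number of fractions (Gy).**

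| Row | 3 | 5 | 6 | 8 | 10 |
|---|---|---|---|---|---|
| Heart | 8.33 | 5.80 | 5.25 | **7.50** | 6.60 |
| Uninvolved liver | 6.40 | 4.80 | 4.33 | 3.63 | 3.20 |
| Stomach, duodenum | 7.40 | 7.00 | 6.17 | 5.00 | 4.35 |
| Bowel | 8.40 | 7.00 | 6.17 | 5.00 | 4.35 |
| Sigma/rectum | 9.40 | 6.80 | 6.17 | 5.13 | 4.40 |
| Oesophagus | 8.40 | 6.80 | 6.00 | 5.00 | 4.35 |
| Kidneys | 2.83 | 2.00 | 1.80 | 1.44 | 1.20 |
| Spinal cord | 7.20 | 5.40 | 4.83 | 4.00 | 3.50 |

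Only the heart row rises anywhere, and only from 6 to 8 fractions.

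**Step 2: ratio of the 8-fraction to the 6-fraction limit.** Heart: 60/31.5 = 1.90. The other eight rows run from 11.5/10.8 = 1.06 (kidneys) to 29/26 = 1.12 (liver).

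**Step 3: the row against itself.** With equal fractions, an 8-fraction plan at its heart limit has given 6 × 7.50 = 45.0 Gy after six fractions, and 45.0/31.5 = 143% of the 6-fraction limit. It is already past that limit at fraction 5 (5 × 7.50 = 37.5 Gy). A 10-fraction plan at its limit is also past it at fraction 5 (5 × 6.60 = 33.0 Gy). The same 6-of-8 comparison in the other rows gives 80% (kidneys, 8.63/10.8) to 84% (liver, 21.75/26). No α/β value is needed here.

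**Step 4: comparison with the tumour dose.** BED = D(1 + D/(10n)) = 100 Gy solves to D = 5n(√(1 + 40/n) − 1).

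- 8 fractions: 40 × (√6 − 1) = 58.0 Gy, below the heart limit of 60 Gy.
- 10 fractions: 50 × (√5 − 1) = 61.8 Gy, below the heart limit of 66 Gy.

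So the heart D0.5cm3 could equal the lowest prescription that reaches BED 100 Gy and still comply.

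**Step 5: values that would fit the 3- to 6-fraction entries.**

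- Holding dose per fraction at or below 5.25 Gy gives ceilings of 8 × 5.25 = 42.0 Gy and 10 × 5.25 = 52.5 Gy.
- Equal BED with 31.5 Gy in 6 fractions means solving D(1 + D/(n·α/β)) = 31.5(1 + 5.25/(α/β)):

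| α/β (assumed) | 8 fractions | 10 fractions |
|---|---|---|
| 2 Gy | 35.5 Gy | 38.8 Gy |
| 3 Gy | 35.1 Gy | 38.1 Gy |
| 10 Gy | 33.8 Gy | 35.5 Gy |

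The ceiling of 42.0 Gy is 42.0/31.5 = 1.33 times the 6-fraction limit, which is still a larger step than in any other row. The equal-BED values for 8 fractions are 1.07 to 1.13 times that limit, close to the other rows.

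**The case against.** The strongest reply is that nothing in the article says a row carries one tolerance across schedules. The limits may be policy values of differing strictness taken from different sources. There is some support for this: at an assumed α/β of 3 Gy the 8- and 10-fraction heart limits have almost equal BED (210 and 211 Gy), while those for 3 to 6 fractions lie between 85 and 94 Gy. That looks more like two sources than one mistyped cell. The table is uneven elsewhere too: the stomach and duodenum limits rise 35/22.2 = 1.58-fold from 3 to 5 fractions. Mixed sourcing may well explain the step. It does not make the limits coherent, and in the stomach and duodenum rows the dose per fraction still falls.

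A second reply is that no row has its own justification and that an article leaves such detail to the full protocol. That stands. The absence of a stated reason is not the fault; the numbers are.

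A third is that a limit is not a target: the other constraints and the treating physician's judgement also apply. That also stands, and it lowers the likely exposure without repairing the row.

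A reader might infer that 60 and 66 Gy are errors and that patients will be over-dosed. The article does not support this. The cited consensus and version 1.4 are not at hand, the 3- to 6-fraction entries could be the ones out of line, and the article gives no frequency of lesions near the heart or of 8- and 10-fraction plans.

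**Conclusion.** The heart row is incoherent as printed. Its limit rises 1.90-fold from 6 to 8 fractions against 1.06- to 1.12-fold elsewhere, and a plan allowed in 8 fractions exceeds the 6-fraction limit by 43% after six. This rests only on the printed values and on equal fractions. At 8 and 10 fractions the limit lies above the minimum dose for tumour BED 100 Gy, so as written it would scarcely protect the heart. Which entries are wrong is not established, and neither is actual over-dose.

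It might also be inferred that the trial's main result is at risk. It is not. The endpoint concerns other organs ("The primary endpoint is defined as the occurrence of treatment-related gastrointestinal or hepatobiliary toxicity of grade III or higher"), arms A and B share the same limits, and the sample size does not use them. For lesions near the heart, the limit could affect whether BED 100 Gy counts as achievable, and so entry to arm C, but the article gives nothing from which to quantify that.

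**What to change.** Check the five heart entries against the cited consensus and protocol version 1.4. Unless 60 and 66 Gy are confirmed as intended, lower them to values that fit the 3- to 6-fraction entries: at most 42.0 Gy in 8 fractions and 52.5 Gy in 10 by the per-fraction cap, or about 34–36 and 35–39 Gy if equal effect with 31.5 Gy in 6 fractions is wanted (α/β assumed 2–10 Gy). The choice within that range is clinical. If the higher limits are confirmed, say so under the table and review whether the 3- to 6-fraction entries are stricter than needed. If only the article differs from version 1.4, correct the article.

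The cost is a source check and a one-row correction. Notice to sites and re-review of 8- and 10-fraction plans with the heart near the target are needed only if those limits prove too high. The downside of lower limits is less dose for a few lesions near the heart.
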